## Discussion

This study protocol presents the design of a randomized controlled clinical trial aimed to evaluate the impact of an MI intervention on the self-care behaviors of people with T1D. We expect the MI-based intervention to improve the doctor-patient relationship and to increase the motivation for self-care, and with it, self-care behaviors. We also expect improvements in glycemic control and increases in self-efficacy and health-related quality of life.

There is evidence that MI can improve self-care in T2D (20, 21). In T1D, to date, however, its application has focused on adolescents, in whom some studies have shown a statistically significant improvement in glycemic control (21–24, 29, 43) but others have not (27). At present, there are no published data on the effect of MI in adults with T1D.

Increasing adherence to self-care is a challenge in a chronic disease such as T1D. An MI-based intervention to replace the traditional interview may improve glycemic control and thus prevent chronic complications in the future. In this study, we aim to evaluate the effect of MI on self-care and HbA1c.

We acknowledge that this study has some limitations. MI is a complex tool to learn; it takes time to manage it correctly, practitioners may not be experts in its use and learned skills tend to wear off. In order to reduce training erosion, regular coaching and feedback will be provided throughout the trial. On the other hand, the same practitioner will apply MI to some patients and the traditional interview to the others (control group), which carries a certain risk of contamination between the study groups. To minimize contamination, participants seen by the same practitioner on the same day were assigned to the same treatment group, which could, of course, lead to some imbalance between the sizes of the groups. To monitor if MI is indeed applied in the intervention group and not in the control group, the sessions will be blindly evaluated at the first and last visits of the study. Finally, not all patients are comfortable with this method of interviewing, a situation that may hinder its application. Regarding outcomes, self-care, the primary outcome, comprises an array of behaviors, which might not accurately reflect the success of MI if change is focused on a single behavior, selected by the patient. The assessment of the achievement of self-defined goals should, at least partially, account for this drawback. Furthermore, some concepts will be examined on an exploratory basis using only a single-item and not a psychometrically tested measure, so these findings should be interpreted as descriptive and with caution. Finally, the sample size of this trial will be able to detect relatively large, clinically relevant changes in the primary and some of the secondary endpoints. However, it might be underpowered to detect smaller, albeit still relevant effect sizes. The low number of healthcare professionals included in the trial, which act as randomization clusters, does not allow the effect associated with the health professionals to be included in the analysis. This could potentially lead to bias, since the variance associated with the healthcare professionals cannot be estimated.

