### Randomization and Blinding

The participants are randomly assigned to the intervention group or control group. A computer-generated randomization list (with a 1:1 ratio) is used for each endocrinologist to prepare the labels indicating the assignment of each patient, which is kept in sealed envelopes, numbered consecutively, and stored at the unit. At the time of inclusion of a patient in the study (appointment 1), the appropriate envelope is chosen and opened to show the endocrinologist the treatment assigned. The randomization is stratified by practitioner and the treatment assigned to the first participant each day is applied to all participants scheduled on that day, in order to facilitate the application of the MI and avoid contamination between treatment groups. To limit possible bias, patients are not informed of the assigned treatment. The informed consent document explains that the study will evaluate the effects of the doctor-patient communication, though without going into detail. The researcher who generated the randomization list and prepared the envelopes for the assignment of the treatment group will not be involved in the treatment or evaluation of the participants; likewise, the researchers who will rate MI compliance and analyze the data will be blind to the treatment allocation.

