#### Professional Training

MI is a set of skills designed to help patients overcome their ambivalence to change by evoking motivation and commitment. Professionals can gain expert experience in this method, for example, through an eight-step program (Motivational Interviewing Network of Trainers- MINT), which can be completed in 16 h.

The three endocrinologists have received structured MI training through theoretical-practical workshops taught by a psychologist with previous training and experience in MI. The workshops, which included didactic instruction and interactive exercises, were divided into two 3- to 4-h sessions and two to four additional 60- to 90-min encounters. The training started 3 months before recruitment, continued until the intervention began and addressed the contents established by MINT (**Table 1**). Interactive exercises included interviews conducted with real playing (i.e., colleagues who proposed something they would like to change, in order to make the practice more realistic), as well as role playing (i.e., using cases that are built on the context of T1D). Furthermore, real-patient interviews were overseen by the psychologist, both directly and through visualization of video recordings, and feedback was provided. Finally, all researchers read the MI book “Motivational interviewing: helping people change” (15). In addition, as a reminder, they were given a magnet on which the main tasks associated with MI are printed, to be put up in a visible place in their unit.

**Table 1 T1:** Contents of the theoretical-practical MI workshop.

*Spirit of MI*	Openness to a new model of thinking and doing with respect to patients. Developing active curiosity to understanding the patient’s perspectives, seeking to evoke the motivation for change in the patient him/herself. The spirit of the MI is based on four principles: collaboration, acceptance, evoking and compassion.
*Acquiring patient-centered counseling skills (OARS: open questions, affirmation, reflection, summary)*	Acquiring skills in the use of patient-centered communication. The key tools of MI are developed: empathy, open questions, affirmation, reflections for feedback, and summaries to take stock.

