### Analysis

Based on the number of patients followed in the clinic and the percentage with an HbA1c above 8%, we estimated that each of the three clinical researchers involved in the trial would be able to recruit around 20 patients in 4 months. With an expected sample size of 60 participants, we would be able to detect inter-group differences of 12.8 points on the SCI-R questionnaire and of 0.85% in HbA1c, with a power of 90% and a two-sided alpha of.05 [assuming an SD of 15 points in the SCI -R and 1% in HbA1c in line with previous studies (5)]. The equivalent detectable differences with a power of 0.8 would be 11 points and 0.74% respectively (calculated with http://hedwig.mgh.harvard.edu/sample_size/js/js_parallel_quant.html). This was an approximate estimation assuming the normality of the variable.

In order to retain most of the patients during follow-up, if someone misses an appointment, the patient is contacted and the visit is re-scheduled. Specific efforts will be made for the final evaluation visit. If a physical appointment cannot be achieved, the questionnaires will be sent and completed by e-mail or, if this is not feasible, the patient with be interviewed by phone. We expect the loss to follow-up to be below 10%.

Intention to treat analysis will be performed: i.e., all randomized participants who have attended at least one intervention (or control) session will be included in the analyses. The main analysis for primary and secondary outcomes, except HbA1c, will be a generalized linear model (GLM) including the intervention arm, the baseline score of the dependent variable and other variables imbalanced at baseline as covariates. The dependent variable will be the post-intervention score. The GLM does not need a normal distribution in the dependent variable (38), although the distribution of the variables will be analyzed using de Shapiro- Wilk test to perform an adequate descriptive analysis. The choice of the link function will depend on the distribution of the variable.

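### The three practitioners are randomisation strata that each treat both arms, so their small number is no reason to leave them out of the models: they can enter as a fixed effect

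*Protocol article*

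**What the plan says.** Protocol article, Randomization and Blinding: "A computer-generated randomization list (with a 1:1 ratio) is used for each endocrinologist", and "The randomization is stratified by practitioner". The same section adds a day rule: "the treatment assigned to the first participant each day is applied to all participants scheduled on that day".

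Professional Training gives the number of practitioners: "The three endocrinologists have received structured MI training".

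The Analysis section defines the model for the primary outcome, and for the secondary outcomes other than HbA1c, as "including the intervention arm, the baseline score of the dependent variable and other variables imbalanced at baseline as covariates". The HbA1c multilevel model follows the same pattern, with time and an arm-by-time interaction added. Neither model names practitioner.

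The Discussion, among the limitations, says that "the same practitioner will apply MI to some patients and the traditional interview to the others". It then gives the reason for leaving practitioner out, which it words as "The low number of healthcare professionals included in the trial, which act as randomization clusters". From this it concludes that so small a number "does not allow the effect associated with the health professionals to be included in the analysis". It adds that bias could follow because the variance due to practitioners cannot be estimated.

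**The concern.** The two descriptions of the practitioners cannot both be right. A randomisation cluster is allocated as a whole to one arm. Here every practitioner has a separate 1:1 list and sees patients in both arms, so practitioner is a stratum crossed with treatment.

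The distinction decides what is feasible. Three units are too few to estimate a between-unit variance, and the Discussion is right on that narrow point. A fixed effect needs no such variance: two indicator variables remove mean differences between three practitioners. The plan therefore accepts a possible bias for a reason that does not apply.

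The primary comparison is at stake. If arms are balanced within practitioner, ignoring the stratum leaves practitioner variation in the residual, so the test is conservative and loses power. If the realised allocation is unbalanced within practitioner, differences between practitioners leak into the treatment estimate. Such differences are plausible: the practitioner delivers the intervention and is the subject of one outcome, satisfaction with the doctor-patient relationship.

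**Working it through.** **1. Inputs.** From the protocol: three practitioners; 60 patients planned and 66 included; SD 15 points for the SCI-R and 1% for HbA1c; two-sided alpha 0.05. Assumed, because the protocol gives no figure: practitioner means of +0.4, 0 and −0.4 SD; 22 patients per practitioner; baseline-outcome correlation 0.5; an effect of 0.6 SD for power; day-blocks of 1 to 3 patients. Power and type I error in steps 4 to 6 come from simulation of the linear model with and without practitioner indicators.

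**2. The plan's own figures.** A two-sample t test with 30 per arm (noncentral t, 58 df) gives detectable differences of 12.77 points and 0.851% at 90% power, and 11.03 points and 0.736% at 80%. The protocol states 12.8, 0.85%, 11 and 0.74%. They reproduce.

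**3. Cost of the fixed effect when arms are balanced within practitioner.** Arm plus baseline leaves N − 3 residual df; two practitioner indicators leave N − 5. SD is held at 15, with no credit for baseline adjustment.
- N = 60: df 57 to 55, critical t 2.0025 to 2.0040, power for 12.8 points 90.13% to 90.09%.
- N = 66: power for 12.8 points 92.69% to 92.66%.

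The loss is under 0.1 point, so three practitioners are not too few.

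**4. Omission with 11:11 in each practitioner.** The estimate is unbiased. Power for 0.6 SD depends on whether the practitioner differences already show at baseline, because the model adjusts for baseline.
- Differences at outcome only: 73.8% without practitioner, 78.2% with (4.4 points lost).
- The same differences at baseline and outcome: 77.0% without, 77.8% with (0.8 points lost).

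**5. Omission under random day-block allocation.** Averaged over the allocation, the estimate is unbiased. Type I error without practitioner is about 5% to 7%. As one example, with 60 patients, no baseline covariate and practitioner explaining 5% to 20% of the outcome variance, it is 6.2% to 7.0%, against 4.9% to 5.5% with the fixed effect.

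**6. Omission with an unfavourable realised split.** Take 15:7, 11:11 and 7:15, aligned with the order of the practitioner means (33 per arm).
- Differences at outcome only: bias = 0.4 × (15 − 7)/33 + (−0.4) × (7 − 15)/33 = 2 × 0.4 × 8/33 = 0.194 SD, and 0.194 × 15 = 2.9 points. Type I error is about 12%.
- Differences also at baseline: adjustment removes a share equal to the within-arm slope of outcome on baseline. The within-arm practitioner variance is 0.16 × 22/33 − (0.4 × 8/33)² = 0.107 − 0.009 = 0.097 after rounding. The slope is (0.5 + 0.097)/(1 + 0.097) = 0.544, so bias = 0.194 × (1 − 0.544) = 0.088 SD, and 0.088 × 15 = 1.3 points. Type I error is about 6%.

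With practitioner in the model, bias is zero and type I error about 5% in both cases.

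**7. Cost of the fixed effect in that split if practitioners do not differ.** The information on the arm contrast is 33 × 33/66 = 16.5 without strata, and 15 × 7/22 + 11 × 11/22 + 7 × 15/22 = 15.05 with them. The ratio is 0.912, so the standard error rises by a factor of 1/√0.912 = 1.047. Power for 0.6 SD falls from 79.1% to 75.4%. This loss comes from the imbalance, not from the 2 df.

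**The case against.** The omission is disclosed, and randomisation protects the estimate on average. Both points stand. Disclosure does not repair a wrong reason, however, and the same limitation would pass into the results paper.

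A reader might infer that the planned test runs at about 12% type I error, or that the estimate is biased by about 0.19 SD. The documents do not support that. Those figures need one split lined up with the practitioner means, and differences absent at baseline. In simulated day-block allocation, a difference between the first and third practitioner at least that large, in that direction, arose in 6.8% of runs. The protocol also says that patients were recruited by their own endocrinologist, so practitioner differences may well already show in baseline SCI-R. It does not settle this, which is why a range is given.

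A reader might also take the Discussion to admit imbalance within practitioner. It admits only that the sizes of the two groups may differ. Unequal totals with similar splits in each practitioner would cause no confounding.

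The planned adjustment for imbalanced variables and the 10% change-in-estimate rule could in principle have brought practitioner in, but the Discussion rules it out expressly. For that reason this is not a detail left to an unseen analysis plan.

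**Conclusion.** The point holds as a contradiction in the protocol and a wrong reason for a modelling choice. Practitioners are strata crossed with arm, and a three-level fixed effect is estimable at either 60 or 66 patients.

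The likely statistical harm is modest. On the stated assumptions it runs from about 1 to 4 points of power when arms are balanced within practitioner, through a type I error of about 5% to 7% over random day-block allocation, to about 6% to 12% for the unfavourable split. These figures depend on the practitioner differences and day-block sizes, neither of which the protocol gives.

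It would go too far to say that including practitioner deals with clustering. The unit that shares one assignment is the practitioner-day. That is a separate issue, which a practitioner fixed effect does not address. Severity: should fix.

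**What to change.** Add practitioner as a three-level fixed effect to the primary model, to the models for the other secondary outcomes and to the HbA1c multilevel model, whether or not it appears imbalanced at baseline.

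Replace the closing limitation in the Discussion with a statement on these lines: randomisation was stratified by practitioner; practitioner is included as a fixed effect; three practitioners are too few to estimate a between-practitioner variance; and the unit sharing one assignment is the practitioner-day, which the practitioner effect does not account for.

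No new data are needed. The cost is 2 df, under 0.1 point of power, if arms are balanced within practitioner. It is about 4 points if arms are as unbalanced as 15:7, 11:11 and 7:15 and practitioners do not differ. The change should be recorded before the treatment allocation is revealed to the analysts.

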## Confidentiality

All study-related information will be stored securely at the study site. All participant information will be stored in locked file cabinets in areas with limited access. All reports, data collection, process, and administrative forms will be identified by a coded ID [identification] number only to maintain participant confidentiality. All records that contain names or other personal identifiers, such as locator forms and informed consent forms, will be stored separately from study records identified by code number. All local databases will be secured with password-protected access systems. Forms, lists, logbooks, appointment books, and any other listings that link participant ID numbers to other identifying information will be stored in a separate, locked file in an area with limited access or in secure, password-protected electronic files.

## Model Consent

The informed consent model used in this study is the one established by the local Ethics Committee.

## Protocol Amendments

Any modifications to the protocol which may impact on the conduct of the study, potential benefit of the patient or may affect patient safety, including changes of study objectives, study design, patient population, sample sizes, study procedures, or significant administrative aspects will require a formal amendment to the protocol. Such amendment will be agreed upon approved by the Ethics Committee of Las Palmas prior to implementation.

## Data Access

All investigators will have access to the trial data sets. Project data sets will be housed locally and will be password protected. Access to cleaned, anonimized data sets will be available to external investigators upon request. The present manuscript does not include data.

## Data Collection Plan: Retention

Participants may withdraw from the study for any reason at any time. In the informed consent model, a section is included for the participant to withdraw their participation if they deem it appropriate. Efforts will be made to minimize drop-outs, as described above.

